This evaluation is the last phase, where health provider and elderly with diabetes will determine the goals is achieved or not. The primary outcomes is the foot self-care behaviour will be improved, the foot self-care behaviour worse, or there is no significant difference of foot self-care behaviour before and after implementation phase. The secondary outcome are level of foot care efficacy expectation, foot care outcome expectation, knowledge on foot care and quality of life. During this phase the effectiveness of the program will be assessed through the questionnaire form of quality of life, knowledge on foot care, foot care efficacy expectation, foot care outcome expectation and foot self-care behaviour.

[figure not shown]

Figure 2.3 The conceptual framework for development and evaluation self-efficacy enhancing program on foot self-care behaviour of elderly with diabetes

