### 3.5.2 Sample size calculation

The sample size estimation, which is carried out using hypothesis testing two population means (Aday & Cornelius, 2006). The data is taken from a previous study conducted by Chen et al. (2011). The baseline score was; mean=32.32 with standard deviation (SD) 6.76, post intervention score has increased to 36.22 with SD 6.95. The hypothesis of no difference is to be tested at the 5% ( $\alpha$ ) 0.05 level of significance and power ( $1-\beta$ ) = 0.80 (80%) (2-tailed). The hypothesis testing two population means sample size estimation as follow:

$$H_0 : \mu_1 = \mu_2$$

$$H_1 : \mu_1 \neq \mu_2$$

$$n = \frac{2\sigma^2 [Z_{1-\alpha/2} + Z_{1-\beta}]^2}{(\mu_1 - \mu_2)^2}$$

$\mu_1$  = estimated mean (larger)

$\mu_2$  = estimated mean (smaller)

$$n = \frac{2(6.76)^2 [1.96 + 0.842]^2}{(36.22 - 32.32)^2}$$

$$n = \frac{(91.40) (7.85)}{15.21}$$

$$n = 47$$

The above sample size formula is valid only for the simple random or systematic random sampling method. This study will employ a cluster sampling design, so it requires a larger sample size to achieve the same precision and power (Aday & Cornelius, (2006).

Therefore, the calculated sample size using the above formula need to be multiplied by the design effect (DEFF). According Aday & Cornelius, (2006), the DEFF =  $1 + (b - 1) roh$ , where  $b$  = cluster size and  $roh$  = rate of homogeneity (intracluster correlation). Assuming a cluster size of 6 and intracluster correlation of 0.05 (Davies et al., 2008), so the DEFF is 1.25. This means that such cluster sampling requires double the sample size of above,  $n = 47 \times 1.25 = 59$  of respondents is needed for each group.

Hence, a total of 71 are considered adequate to recruit for a dropout rate and potential of attrition (20%). Thus, total 142 eligible criteria of the respondents is needed to be approached in order to retain 118 respondents (59 respondents per group) at the end of the study.

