### **3.9 Data analysis/management**

The data collected will be analysed using the descriptive and inferential statistics. Statistical Packages for the Social Sciences version 22 for Windows will be used. Data screening will be performed to check the accuracy of data entry and to make sure that there is no missing value. Statistical test used are descriptive and inferential test. The level of significance will be set at  $p < 0.05$  (two-tailed) for all inferential analysis. The statistical report and conclusion will be written using APA style format.

Firstly, factor analysis will be used as a data reduction techniques to reduce a large number of variables to smaller set underlying factors that can summarizes the essential information contained in the variable and this procedure called as factor analysis (Coakes & Steed, 2003). The responses to the items of FCCS, and FCOE will be subjected to principal component analysis to identify underlying dimensions or factors. A threshold of 0.60 will be used to determine which statements are considered to be part of a factor. Internal consistency or reliability acceptable results for each factor and items that will be tested by Cronbach's alpha is acceptable as the alpha values for all the factors are above 0.80.

The demographic data and clinical characteristics will be analysed with descriptive statistics. The mean and standard deviation (SD) for continuous variables and the count (n) and percentages (%) for the dichotomous or nominal data (categorical data) will be calculated.

Meanwhile, to answer the hypothesis testing, an inferential statistics such as chi-square, mixed design analysis of variance (ANOVA) and repeated measure analysis of variance (RM-ANOVA) (if all statistical assumption for parametric tests are meets) will be used to compare the effectiveness before and after the intervention program. Table 3.5 showed the type of analysis that will used for each research objectives.

Table 3.5 Type of analysis based on research objectives.

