| 
Objective 2
 
To determine the effects of self-efficacy enhancing program on quality of life, knowledge on diabetes foot care, foot care efficacy expectation, foot care outcome expectation and foot self-care behaviour of elderly with diabetes between group (intervention and control) at Time 1 (before the intervention education program), Time 2 (four weeks after the intervention education program) and Time 3 (12 weeks after the intervention education program)
 | 
Mixed between-within subjects ANOVA to examine the differences between two independent groups (intervention and control) while subjecting participants to repeated measures between T1, T2 and T3.
                                                                            |
| 
Objective 3
 
To determine the effects of self-efficacy enhancing program on quality of life, knowledge on diabetes foot care, foot care efficacy expectation, foot care outcome expectation and foot self-care behaviour of elderly with diabetes within group (intervention and control) at Time 1 (before the intervention education program), Time 2 (four weeks after the intervention education program) and Time 3 (12 weeks after the intervention education program)
  | 
RM-ANOVA to examine the differences in the outcomes between T1, T2 and T3. F tests with paired t tests to identify when changes in outcomes will take place.
                                                                                                                  |

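### The between-group ANOVA uses the pre-intervention score as one of its outcomes, and no contrast or missing-data rule is fixed for the primary outcome; a baseline-adjusted week-12 comparison would settle this with data already collected

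*Combined protocol and SAP*

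**What the plan says.** Section 3.9, Table 3.5 (Objective 2) gives one between-group analysis for all five outcomes: a "Mixed between-within subjects ANOVA to examine the differences between two independent groups (intervention and control"), with T1, T2 and T3 as the repeated measures. Section 1.5.2 defines T1 as before the programme, T2 as four weeks after it and T3 as twelve weeks after it.

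Section 2.6 identifies the primary variable: "The primary outcomes is the foot self-care behaviour will be improved". Section 3.10 agrees. Neither section, nor Table 3.5, names a deciding visit or model term. The only follow-up tests that locate change in time are paired t tests, and these belong to the within-group objective.

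On incomplete data, Section 3.9 says only that screening is meant "to make sure that there is no missing value". Section 3.5.2 allows for 20% attrition, approaching 142 residents in order to keep 118. The sample size there is for a two-sided comparison of two means, multiplied by a design effect.

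**The concern.** Homes are randomised, so the expected T1 difference between arms is zero. The ANOVA supplies two terms that could be read as the between-group result, and each has a weakness.

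- **Group main effect.** It averages the arm difference over T1 to T3. If the effect is the same at T2 and T3, the average is two thirds of the true effect. It also carries any chance baseline difference between the three homes in each arm.
- **Group-by-time term.** It removes a stable baseline difference, but as a 2-df F test it gives neither the timing nor the direction of the difference.

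With neither term designated, the choice could be made after the results are seen. A classical repeated-measures ANOVA also drops, by default, anyone missing a visit. A resident seen at week 4 but lost by week 12 would then contribute nothing. At stake are the clarity of the primary conclusion, avoidable loss of power, and reliance on completers.

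**Working it through.** **Inputs from Section 3.5.2.** The source scores are "mean=32.32 with standard deviation (SD) 6.76, post intervention score has increased to 36.22 with SD 6.95". The plan uses difference 36.22 − 32.32 = 3.90 and SD 6.76, with two-sided alpha 0.05 and 80% power.

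**Reproducing the plan's figure.**
- n = 2 × 6.76² × (1.96 + 0.842)² / 3.90² = 47.18, stated as 47.
- 47 × 1.25 = 58.75, so 59; 59 × 1.2 = 70.8, so 71; 2 × 71 = 142.
- Planned loss: 142 − 118 = 24 residents.

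**Comparing the tests.** I take the plan's own effective n = 47.18 per arm (59 divided by the design effect of 1.25) and d = 3.90/6.76 = 0.577, so √(n/2) = 4.857. Assumptions not in the documents: residents independent, equal variance and equal correlation r between all visits, the full effect present at both T2 and T3 (a step effect), and r = 0.3, 0.5 or 0.7.

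- Group main effect: noncentrality (2/3)d / √((1+2r)/3) × √(n/2). At r = 0.5: 0.385/0.816 × 4.857 = 2.29.
- Group-by-time: λ = n d² / (3(1−r)), F with 2 and 2(2n−2) df. At r = 0.5: 47.18 × 0.333/1.5 = 10.47.
- Baseline-adjusted week 12: noncentrality d / √(1−r²) × √(n/2). At r = 0.5: 0.577/0.866 × 4.857 = 3.24.

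| Test | r = 0.3 | r = 0.5 | r = 0.7 |
|---|---|---|---|
| Group main effect | 72% | 62% | 54% |
| Group-by-time, 2 df | 68% | 83% | 97% |
| Baseline-adjusted week 12 | 83% | 89% | 97% |

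**Sensitivity to r.** At r = 0.8, group-by-time and the adjusted test both exceed 99%. At r = 0.1 the main effect has 83% against 80% for the adjusted test; the two cross at about r = 0.15.

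**Sensitivity to the shape of the effect.** If only one third of the effect is present at week 4, group-by-time falls to 56/72/92% and the main effect to 39/33/28%. The adjusted week-12 test is unchanged.

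**Allowing for the homes.** The comparison above ignores that only six homes are randomised. I simulated three homes of 20 per arm with the plan's intracluster correlation of 0.05, and assumed that home effects correlate 0.5 or 0.8 between visits. A valid baseline-adjusted test on home means (about 4 df) has roughly 46 to 72% power for r = 0.3 to 0.7, against 40 to 42% without adjustment. Baseline adjustment of individual residents with no term for home rejects a true null 11 to 22% of the time.

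**The case against.** The strongest reply is that the group-by-time term is the natural reading. Section 3.9 describes the tests as comparing effectiveness before and after the programme. That term cancels a stable baseline difference and reaches 83% at r = 0.5 and 97% at r = 0.7, above the 80% target. A planned 1-df contrast inside the same ANOVA (mean of T2 and T3 minus T1) has noncentrality d / √(1.5(1−r)) × √(n/2), which gives 78/90/99%. So, for a step effect, much of the shortfall comes from naming no contrast rather than from treating T1 as a response. This stands. It strengthens the case for naming one contrast and weakens any claim that baseline adjustment always wins.

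Three stronger readings are tempting, and the documents do not support them.

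- **That the plan specifies a complete-case analysis.** It does not. No missing-data rule is written; listwise deletion is what the named method does by default.
- **That dropping lost residents takes power below plan.** The 59 per group is already the number expected at the end. The cost is possible bias and unused week-4 data, and the number of lost residents who would have a T2 questionnaire is unknown.
- **That chance baseline imbalance goes uncorrected whichever term is used.** This is true of the group main effect only.

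The documents give no correlation between baseline and week 12. The one related figure, a two-week test-retest coefficient of 0.92 in Table 3.2, means high values cannot be excluded.

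**Conclusion.** The point holds with limits. Two findings need no assumption about correlation: no term or visit is designated for the primary outcome, and no missing-data rule exists despite a planned loss of 24 residents. T1 as a response level is also plain from Table 3.5.

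The power gain is conditional. Under the stated assumptions it is about 15 points over group-by-time at r = 0.3 and 6 at r = 0.5. For a step effect it is gone by about 0.7 to 0.8; it is larger and lasts longer if the effect builds slowly. Against the main effect the gain is 11 to 43 points for r = 0.3 to 0.7, but it reverses below about 0.15.

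A reader might take 83/89/97% as the power the trial would have after the change. It is not: those values assume independent residents. A valid analysis of three homes per arm stays below 80% in the settings simulated, although baseline adjustment still improves it.

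**What to change.** Name one primary contrast: the between-arm difference in DFSBS at week 12. Estimate it from a linear mixed model with:

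- T2 and T3 DFSBS as outcomes and T1 DFSBS as covariate;
- arm, visit and arm-by-visit;
- random effects for resident and RSK;
- a small-sample degrees-of-freedom correction (about 4 df for the arm effect), by Kenward-Roger or Satterthwaite. A baseline-adjusted analysis of home-level means is an acceptable alternative.

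Include every resident with at least one post-baseline questionnaire, in the arm to which their RSK was randomised, and report by arm those who have none. State this as the missing-data rule in place of the screening sentence. Use the same model for each secondary outcome with its own T1 value.

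The cost is a rewording of Section 3.9 and Table 3.5. All scales are already scheduled at T1, week 4 and week 12, so no residents, visits or forms are added. The downsides are slightly more analysis work, possibly outside the planned SPSS procedure, and little or no power gain over group-by-time if the baseline correlation proves high.

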### **1.5.2 Specific objectives**

- 1) To determine the:
  - demographic data of respondents
  - clinical characteristics of respondents
  - foot self-care behaviour of respondents
  - foot care efficacy expectation of respondents
  - foot care outcome expectation of respondents
  - knowledge on diabetes foot care of respondents
  - quality of life of respondents
- 2) To develop and to implement the self-efficacy enhancing program on foot self-care behaviour of elderly with diabetes
- 3) To determine the effects of self-efficacy enhancing program on quality of life, knowledge on diabetes foot care, foot care efficacy expectation, foot care outcome expectation and foot self-care behaviour of elderly with diabetes between group (intervention and control) at Time 1 (before the intervention education program), Time 2 (four weeks after the intervention education program) and Time 3 (12 weeks after the intervention education program)
- 4) To determine the effects of self-efficacy enhancing program on quality of life, knowledge on diabetes foot care, foot care efficacy expectation, foot care outcome expectation and foot self-care behaviour of elderly with diabetes within group (intervention and control) at Time 1 (before the intervention education program), Time 2 (four weeks after the intervention education program) and Time 3 (12 weeks after the intervention education program)

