| Borges &
Ostwald
(2008)

3-arm RCTs

The U.S                    | Improving foot
self-care
behaviors with
Pies Sanos

Theory: Self-
efficacy                                                                        | To improve diabetes
self-efficacy and foot
self-care behaviors in
adult patients with type
2 diabetes who lived in
a predominantly
Mexican American
community

N= 55 (IG1), 55 (IG2)
57 (CG) | Approach: Group, health setting

IG1 (risk assessment group): Time: 5-min foot risk
assessment using a monofilament
IG2 (intervention group): Time: 5-min foot risk
assessment using a monofilament and a 15-min
brief foot self-care intervention.
Content: The educational and behavioral
strategies designed to increase self-efficacy for
foot self-care and ultimately change foot self-care
behaviors. Pictorial form, "Foot Care for People
With Diabetes"
CG: usual care
Delivered by the researchers | Baseline - 1 month

Outcome:
Knowledge
Self-efficacy
Self-care
Acculturation
Foot self-care
observation                                               | PO:
There was a significant
difference in foot self-
care behaviors between
groups ( $p < 0.05$ )

Improved foot self-care
behaviors within the CG,
( $p < 0.05$ ) and the IG2
( $p < 0.01$ )

SO: not mentioned                             | The
intervention
improved
diabetes foot
self-care
behaviours          | Good                    |

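### Table 3.5, Objective 3 treats change within an arm as an effect of the program, and no between-arm contrast is named as deciding effectiveness

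*Combined protocol and SAP*

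**What the plan says.** Section 1.5.2 lists a between-group objective (3) and a within-group objective (4). Table 3.5 in section 3.9 renumbers them as Objectives 2 and 3. Both rows are worded as establishing effects of the program on the same five outcomes.

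- **Objective 2, between arms:** "Mixed between-within subjects ANOVA to examine the differences between two independent groups (intervention and control", with T1, T2 and T3 as repeated measures.
- **Objective 3, within arms:** the effects are sought in "elderly with diabetes within group (intervention and control) at Time 1" and the later times. The method is "RM-ANOVA to examine the differences in the outcomes between T1, T2 and T3", followed by "F tests with paired t tests to identify when changes in outcomes will take place".

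The text of section 3.9 introduces chi-square, mixed ANOVA and RM-ANOVA together as tests that "will be used to compare the effectiveness before and after the intervention program". The 0.05 level is "two-tailed) for all inferential analysis", and no multiplicity adjustment is mentioned. The closing phase of the framework in section 2.6 classes foot self-care behaviour as better, worse or not significantly different before and after implementation. It does not refer to the control arm.

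No section says that the within-arm tests are descriptive, that the group-by-time interaction is the test of effectiveness, or which result prevails if the two objectives disagree.

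**The concern.** A before-after change in one arm combines whatever the program does with everything else that changes scores over 12 weeks. The control arm has such influences too. Under section 3.7.2 and Table 3.4 it completes the same questionnaires at baseline, week 4 and week 12, receives researcher visits at weeks 4 and 12, and is given a health reminder at the last visit. Section 1.7 anticipates higher scores from information obtained elsewhere. Section 2.3.6 itself notes that one-group studies can only compare before with after.

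The literature table shows that control arms can move: the three-arm self-efficacy trial reports improved foot self-care "behaviors within the CG" at p < 0.05. As the same table summarises it, another study's intervention arm rose from 12.47 to 43.17 with no significant difference between groups, yet section 2.3.6 lists that study among those showing improved foot self-care.

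Because Objective 3 carries the same wording about effects as Objective 2, an investigator following the plan could report a program effect from the intervention arm alone when controls had improved equally.

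**Working it through.** **Inputs**
- Section 3.5.2: means 32.32 and 36.22 (difference 3.90), SD 6.76, two-sided alpha 0.05, power 0.80, design effect 1.25, 20% added for dropout, 59 retained per arm.
- Table 3.5: three time points, five outcomes, two arms.
- Assumed, because the plan gives no figure: correlation between time points r = 0.5, range 0.3 to 0.7.

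**The plan's own figure first.** n = 2 × 6.76² × (1.96 + 0.842)² / 3.90² = 47.18, stated as 47. Then 47 × 1.25 = 58.75, rounded to 59; 59 × 1.20 = 70.8, rounded to 71; 2 × 71 = 142. The stated sample size reproduces, so 59 per arm is used below.

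**One-arm test when the program does nothing.** Let both arms have the same true gain d from T1 to T3. The SD of the within-person change is 6.76 × √(2(1 − r)), which is 6.76 at r = 0.5. Its standard error is 6.76/√59 = 0.880. The noncentrality is d/0.880: 1.14, 2.27 and 4.43 for d = 1.0, 2.0 and 3.9. With the noncentral t distribution on 58 degrees of freedom, the probability p of a significant improvement in the intervention arm is:

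| Common gain | r = 0.3 | r = 0.5 | r = 0.7 | Between-arm test of change (simulated, r = 0.5) |
|---|---|---|---|---|
| 1.0 | 16% | 20% | 30% | 4.6% |
| 2.0 | 47% | 61% | 82% | 5.0% |
| 3.9 | 96% | 99% | 100% | 5.0% |

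The last column comes from 4,000 simulated trials per gain with independent respondents, so clustering by home is ignored. Its Monte Carlo standard error is √(0.05 × 0.95/4,000), about 0.3 percentage points. The same simulations gave 20%, 60% and 99% for the one-arm test at r = 0.5. Running the T1-T3 paired test only after a significant F test still gave 14%, 53% and 99%.

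**Intervention significant, control not.** With equal gains and independent arms this has probability p(1 − p). Its maximum is 0.5 × 0.5 = 25%. At r = 0.5 it is 0.200 × 0.800 = 16% at a gain of 1.0, 0.608 × 0.392 = 24% at 2.0, and 0.992 × 0.008 = about 1% at 3.9.

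**Multiplicity, one outcome in one arm, no true change.** Three paired t tests run without a gate gave at least one significant result in 12.7% of simulations (r = 0.5). Run only after a significant F test, they gave 5.0%.

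**The case against.** The strongest reply is that the randomised comparison is in the plan. The row above Objective 3 specifies a mixed ANOVA between arms for all five outcomes, and section 1.5.2 lists the between-group objective first. The control arm is analysed in the same way, so equal improvement would be visible. This stands, and it rules out the inference that the trial bypasses its randomisation. It does not answer the narrower point: two objectives carry the same claim and no rule says which one settles it.

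Other readings go further than the documents allow.

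- **A decision rule of significant in one arm, not in the other.** No section adopts it. The 25% is the ceiling of p(1 − p), not a prediction; at the planning gain of 3.9 the figure is about 1%.
- **Paired t tests run on every pair without correction.** That is inferred from silence. The wording of Objective 3 can equally mean follow-up after a significant F test, which holds error near 5% per outcome and arm, though not across five outcomes and two arms.
- **Regression to the mean.** The eligibility criteria in section 3.5.3 do not select on foot self-care score, so no shift in the arm mean follows from selection.
- **The cited three-arm trial as a false effect.** The same table entry also reports a significant difference between groups. It shows only that a usual-care arm can improve.
- **The section 3.9 sentence on before and after.** It covers all the listed tests, so it is weak evidence about the within-arm ones.

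**Conclusion.** The point holds in limited form. Objective 3 presents within-arm change as an effect of the program, section 2.6 frames the primary outcome in the same way, and the plan neither limits those tests to description nor names the deciding between-arm contrast. With no program effect and equal gains, the intervention-arm test is positive in about 20% to 99% of trials over gains of 1.0 to 3.9, against about 5% for a between-arm test of change.

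These figures rest on 59 analysed per arm, SD 6.76 at each time, the assumed correlation of 0.5 and no clustering. The 3.9 is the plan's own before-after planning gain and is the upper end for a control arm; the documents give no expected control gain. Multiplicity is secondary: about 13% per outcome and arm if the paired tests are ungated, about 5% if gated. This should be changed before analysis. It does not mean that the trial lacks a between-arm analysis.

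**What to change.** 1. Reword objective 4 in section 1.5.2 and Objective 3 in Table 3.5 as descriptive: mean change from T1 to T2 and from T1 to T3 in each arm, with 95% confidence intervals. Label any within-arm p-values as secondary and not evidence of effect.
2. State in section 3.9 that conclusions about the program rest on one named between-arm contrast. Use either the group-by-time interaction of the Objective 2 model, or the between-arm differences at T2 and T3 from a separately specified model adjusted for the T1 score. The second needs its own model, because the Objective 2 ANOVA has T1 as a repeated measure and does not yield baseline-adjusted differences.
3. Account for home as the unit of allocation (three homes per arm) in whichever contrast is chosen.
4. Align the evaluation wording in section 2.6 with that contrast, and use it to answer when changes occur.

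The cost is wording and a small change to the analysis model. No extra data are needed.
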